### Randomisation and enrolment procedure

Patients will be enrolled by invitation, if they fulfil all inclusion criteria and no exclusion criteria. A randomisation schedule will be generated by the website Randomization.com (http://www.randomization.com). Clinical trial materials will be packed and Qualified person (QP) certified by a contracted NHS Pharmacy, according to the randomization schedule (under Article 13 of EU directive 2001/20/EC). The medication bottles and randomization schedule will be shipped to the site pharmacy, following regulatory approvals. The randomisation schedule will be strictly controlled and remain in the pharmacy site file for emergency unblinding purposes. These features ensure the study has pharmacy controlled allocation concealment. Medication bottles will be dispensed in sequential number order, with each subject receiving Period 1 and Period 2.

Unblinding during the trial will only be undertaken in the event of a SAE or Suspected Unexpected Serious Adverse Reaction (SUSAR), or disease progression, under the authorization of the principal investigators. Emergency unblinding will be managed by North Bristol NHS Trust Pharmacy Department, according to standard operating procedure (CT/011). The study includes three MS-specific Expanded Disability Status Scale (EDSS) tests (pre-treatment and at the end of each treatment period) to monitor disease severity. Interim analysis will evaluate outcomes of the first treatment period. The analyses will provide the content of a blinded report to the Trial Management Group (TMG). If issues of safety emerge, the TMG will be empowered to request unblinded data.

### Interaction with other drugs

The subjects will not be permitted to useSedative medications (CNS depressants). Taking melatonin along with sedative medications might cause excessive sleepiness. Sedative medications include clonazepam (Klonopin), lorazepam (Ativan), phenobarbital (Donnatal), zolpidem (Ambien), and others. Patients will be instructed to discuss with the trial co-ordinating office before starting such medications.

Caution will be advised for the following;Birth control pills (Contraceptive drugs). Taking melatonin along with birth control pills might increase the effects and side effects of melatonin. Effective methods of birth control for females of child-bearing potential are an inclusion criterion of the MeNiMS study; the trial co-ordinating office records method of contraception on the Case Report Form (CRF).Fluvoxamine (Luvox). Taking fluvoxamine (Luvox) can increase the amount of melatonin that the body absorbs. Taking melatonin along with fluvoxamine (Luvox) might increase the effects and side effects of melatonin. Patients will be instructed to discuss with the trial co-ordinating office before starting fluvoxamine.Medications for diabetes (Antidiabetes drugs). Melatonin might increase blood sugar, and thereby might decrease the effectiveness of diabetes medications. The dose of diabetes medication might need to be changed. Some medications used for diabetes include glimepiride (Amaryl), glyburide (DiaBeta, Glynase PresTab, Micronase), insulin, pioglitazone (Actos), rosiglitazone (Avandia), chlorpropamide (Diabinese), glipizide (Glucotrol), tolbutamide (Orinase), and others.Medications that decrease immune system function (Immunosuppressants). Melatonin might reduce the efficacy of immunosuppression. The trial co-ordinating office will discuss immunosuppression therapy with relevant patients.Medications that slow blood clotting (Anticoagulant/Antiplatelet drugs). Melatonin might slow blood clotting. Taking melatonin along with medications that also slow clotting might increase the chances of bruising and bleeding. Some medications that slow blood clotting include aspirin, clopidogrel (Plavix), diclofenac (Voltaren, Cataflam, others), ibuprofen (Advil, Motrin, others), naproxen (Anaprox, Naprosyn, others), dalteparin (Fragmin), enoxaparin (Lovenox), heparin, warfarin (Coumadin), and others. The trial co-ordinating office will discuss anticoagulation therapy with relevant patients.Nifedipine GITS (Procardia XL). Taking melatonin might decrease the effectiveness of nifedipine GITS for lowering blood pressure.Verapamil (Calan, Covera, Isoptin, Verelan). Verapamil (Calan, Covera, Isoptin, Verelan) can increase how quickly the body metabolises melatonin. Taking melatonin along with verapamil (Calan, Covera, Isoptin, Verelan) might decrease the effectiveness of melatonin.

### Dispensing and accountability

Dispensing, checking and collection is according to North Bristol NHS Trust Pharmacy standard operating procedures (CT/008).

Site staff will count study drug back in at return clinic visits, and remind the subject that they need to bring all their study drug and packaging back with them.

### Pharmacovigilance

Melatonin appears to cause very few side-effects in the short term, up to three months, when healthy people take it at low doses. A systematic review in 2006 looked at safety with melatonin usage for secondary sleep disturbances and sleep disorders accompanying sleep restriction [19]. The study concluded that melatonin is safe with short term use.

Unwanted effects in some people, especially at high doses (3 mg/day or more) may include: headaches, nausea, next-day grogginess or irritability, hormone fluctuations, vivid dreams or nightmares, gastrointestinal irritation, reduced blood flow and hypothermia. While no large, long-term studies that might reveal side-effects have been conducted, there do exist case reports about patients having taken melatonin for months. Melatonin can cause somnolence (drowsiness), and, therefore, caution should be shown when driving, operating machinery, etc.

#### Definitions

Adverse Event (AE): any untoward medical occurrence in a patient or clinical trial subject administered a medicinal product and which does not necessarily have a causal relationship with this treatment. An AE can therefore be any unfavourable and unintended sign (including an abnormal laboratory finding), symptom, or disease temporally associated with the use of an investigational medicinal product (IMP), whether or not considered related to the IMP.

Adverse Reaction (AR): all untoward and unintended responses to an IMP related to any dose administered. All AEs judged by either the reporting investigator or the sponsor as having reasonable causal relationship to a medicinal product qualify as adverse reactions. The expression “reasonable causal relationship” means to convey in general that there is evidence or argument to suggest a causal relationship.

Unexpected Adverse Reaction: an AR, the nature or severity of which is not consistent with the applicable product information (e.g., investigator’s brochure for an unapproved investigational product or summary of product characteristics (SmPC) for an authorised product). When the outcome of the adverse reaction is not consistent with the applicable product information this adverse reaction should be considered as unexpected. Side effects documented in the SmPC which occur in a more severe form than anticipated are also considered to be unexpected.

Serious Adverse Event (SAE) or Serious Adverse Reaction: any untoward medical occurrence or effect that;Results in deathIs life-threatening – refers to an event in which the subject was at risk of death at the time of the event; it does not refer to an event which hypothetically might have caused death if it were more severeRequires hospitalization, or prolongation of existing inpatients’ hospitalizationResults in persistent or significant disability or incapacityResults in a congenital anomaly or birth defect

Medical judgement should be exercised in deciding whether an AE/AR is serious in other situations. Important AE/ARs that are not immediately life-threatening or do not result in death or hospitalization but may jeopardise the subject or may require intervention to prevent one of the other outcomes listed in the definition above, should also be considered serious.

Suspected Unexpected Serious Adverse Reaction (SUSAR): any suspected adverse reaction related to an IMP that is both unexpected and serious.

#### Causality

Most adverse events and adverse drug reactions that occur in this trial, whether they are serious or not, will be expected treatment-related toxicities due to the drugs used in this trial. The assignment of the causality will be made by the investigator responsible for the care of the participant using the definitions in the table below. If any doubt about the causality exists the local investigator will notify the Chief Investigator.

### Relationships

**Unrelated**. There is no evidence of any causal relationship

**Unlikely**. There is little evidence to suggest there is a causal relationship (e.g. the event did not occur within a reasonable time after administration of the trial medication). There is another reasonable explanation for the event (e.g. the participant’s clinical condition, other concomitant treatment).

**Possible**. There is some evidence to suggest a causal relationship (e.g. because the event occurs within a reasonable time after administration of the trial medication). However, the influence of other factors may have contributed to the event (e.g. the participant’s clinical condition, other concomitant treatments).

**Probable**. There is evidence to suggest a causal relationship and the influence of other factors is unlikely.

**Definitely**. There is clear evidence to suggest a causal relationship and other possible contributing factors can be ruled out.

**Not assessable**. There is insufficient or incomplete evidence to make a clinical judgment of the causal relationship.

#### Reporting procedures

##### Non serious AR/AEs

All such toxicities, whether expected or not, will be recorded in the toxicity section of the relevant case report form and sent to the trial coordination centre within one month of the form being due.

##### Serious AR/AEs

Fatal or life threatening SAEs and SUSARs will be reported on the day that the local site is aware of the event. The SAE form asks for nature of event, date of onset, severity, corrective therapies given, outcome and causality (i.e. unrelated, unlikely, possible, probably, definitely). The responsible investigator will sign the causality of the event. Additional information will be sent within 5 days if the reaction has not resolved at the time of reporting.

An SAE form will be faxed to the trial coordination centre for all SAEs within 24 h. However, relapse and death due to MS, and hospitalizations for elective treatment of a pre-existing condition do not need reporting as SAEs.

In the case of suspected unexpected serious adverse reactions (SUSARs), the staff at the site will: Complete the SAE case report form & send it immediately (within 24 h, preferably by fax), signed and dated to the trial coordination centre together with relevant treatment forms and anonymised copies of all relevant investigations.

The trial coordination centre will notify the MHRA, REC and the Sponsor of all SUSARs occurring during the trial according to the following timelines; fatal and life-threatening within 7 days of notification and non-life threatening within 15 days. All investigators will be informed of all SUSARs occurring throughout the trial.

Local investigators will report any SUSARs and/or SAEs as required by their Local Research Ethics Committee and/or Research & Development Office.

Subjects will have a safety follow-up at 2 – 4 weeks by telephone call. If there has been an AE, the participant will be followed up until the AE resolves, or resolves with sequelae for a limit of 3 months and will remain under clinical management as needed.

### Loss to follow-up

Subjects lost to follow up will be contacted by telephone call and subsequently through their general practitioner. If they can be contacted, they will then be managed as per withdrawals. Records relating to all patients lost to follow up will be retained and archived according to the overall study protocol.

### Trial closure

The end of the crossover study will be defined as the point at which all study subjects have completed the data collection visits and follow up.

The trial will be closed prematurely if the TMG recommends it to the steering committee on the grounds of safety or futility. Interim analysis will be undertaken following the first treatment period. The analysis will provide the content of a blinded report to the TMG, which will consider safety/adverse effects, and assess the possibility of futility. If issues of safety emerge, the TMG will be empowered to request unblinded data. As it deems necessary, the TMG will make recommendations to the sponsor on further study conduct, including continuing, terminating, or modifying the trial. Early termination will result if clinically significant unexpected adverse effects are seen, or if the study is deemed futile, or if the beneficial effect is so obvious that curtailment can occur.

The Sponsor (Research & Innovation Department North Bristol NHS Trust) will monitor the study to ensure compliance with Good Clinical Practice procedures.

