### Statistics and data analysis

Sample size is informed by (a) a previous study of melatonin, which showed a reduction in nocturia episodes of 0.5 per night to be clinically significant [7], (b) comparable crossover investigations using melatonin in other populations [21], (c) crossover trial methodology [22], and (d) project feasibility. For a two-sided test, using standard levels of statistical significance (alpha = 0.05), a sample size of *n* = 21 complete data sets would have 80% power to detect a medium to large effect size (Cohen’s d = 0.65) with 80% power, and a sample size of *n* = 34 would be needed for a medium effect size (Cohen’s d = 0.5).

The balanced two group, two period, two sequence, double-blind, randomised crossover design with wash-out period comparing treatment to control, ranks highly in the hierarchy of designs. The analyses of the resultant data under this AB/BA design may proceed using well known statistical techniques (e.g. [23]).

Primary analyses will focus on nocturia episodes per night and volume voided per night determined pre- and post-treatment for the two conditions (melatonin, placebo) within each period. The experimental structure therefore has a two by two fully repeated measures structure. The design has been structured with a large washout period and it is anticipated that there will be no carryover effects on physiological and psychological outcomes. This assumption will be tested. Period effects should also be absent and this supposition will also be tested and analysis will proceed to estimate treatment effects robust to any period effect (CROS analysis). It is recognised that outcome data may be skewed for this population and nonparametric or bootstrapped inference will be used as appropriate. Analyses will proceed on an Intent-to-Treat basis.

A missing data analysis will also be performed and sensitivity of statistical conclusions to missingness will be undertaken using standard imputation techniques. Data integrity checks will be undertaken prior to inferential analysis including a detailed graphical and summary statistics descriptive analysis. The statistician will be masked to prevent ascertainment bias. All analyses, and the reporting of analyses, will be undertaken in the spirit and guidance of the CONSORT guidelines.

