### Monitoring

The TMG will consider safety/adverse effects, and assess the possibility of futility. If issues of safety emerge, the TMG will be empowered to request unblinded data. As it deems necessary, the TMG will make recommendations to the sponsor on further study conduct, including continuing, terminating, or modifying the trial. Early termination will result if unexpected adverse effects are seen, or if the study is deemed futile, or if the beneficial effect is so obvious that curtailment can occur.

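### Early closure for futility or obvious benefit is written in, but the only interim described is a blinded report on first-period data, which cannot soundly support either decision

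*Protocol article*

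**What the plan says.** One interim analysis is described. Under Randomisation and enrolment procedure: "Interim analysis will evaluate outcomes of the first treatment period". Under Trial closure: "The analysis will provide the content of a blinded report to the TMG". Risk assessment repeats both points. Under Monitoring: "The TMG will consider safety/adverse effects, and assess the possibility of futility". Unblinded data are mentioned as something the TMG may ask for if a safety issue emerges; no other trigger is given.

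Trial closure gives the grounds for stopping twice. The first statement has the TMG recommending closure for safety or futility. The second, a few sentences later and again under Monitoring, says early termination will result for unexpected adverse effects, "or if the study is deemed futile, or if the beneficial effect is so obvious that curtailment can occur".

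The sample size paragraph (Statistics and data analysis) reads "For a two-sided test, using standard levels of statistical significance (alpha = 0.05" and makes no mention of an interim look. An independent Data Monitoring Committee (DMC) is described as an aim and is given no stated part in the stopping decision.

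**The concern.** Both futility and obvious benefit are judgements about the difference between melatonin and placebo. The TMG is told to reach them, yet the report it receives is blinded and the one unblinding trigger concerns safety. As written, the rule cannot be followed soundly. A statistical analysis plan could add boundaries, but it would not remove the conflict between these protocol statements, or the conflict within Trial closure over whether benefit is a ground at all.

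If the blind were lifted, or groups shown under codes, the data would still be from period 1 only. That is a parallel-group comparison, without the within-patient precision on which the sample size rests. At stake are a futility stop in a trial whose treatment works as planned, and a claim of benefit made on a weak contrast with no threshold stated in this document.

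**Working it through.** **Inputs from Statistics and data analysis.** Two-sided alpha 0.05; n = 21 at d = 0.65 ("21 complete data sets would have 80% power to detect a medium to large effect size"); n = 34 at d = 0.5 ("34 would be needed for a medium effect size"); balanced AB/BA design. **Assumed, because the article does not give them:** the correlation rho between two charts from the same patient, taken as 0.3 to 0.8 and equal for baseline and both periods; equal SDs; all patients having finished period 1 at the look; and any interim efficacy threshold.

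**1. The plan's own figures.** Paired t-test, noncentrality d√n, n − 1 degrees of freedom:
- n = 21: 0.65 × √21 = 2.98, power 80.9%.
- n = 34: 0.5 × √34 = 2.92, power 80.8%.

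Both reproduce as a single-look, within-patient test at 0.05. Nothing is set aside for an interim test.

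**2. Pooled blinded data.** A true between-patient effect d_b inflates the pooled SD by √(1 + d_b²/4). At rho = 0.5, d_b equals the paired d:
- n = 21: √(1 + 0.65²/4) = 1.05, while the relative standard error of an SD is 1/√(2 × 20) = 16%.
- n = 34: √(1 + 0.5²/4) = 1.03, against 1/√(2 × 33) = 12%.

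Over rho 0 to 0.8 the inflation is 1% to 10%. The planned effect would be lost in the noise.

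**3. Coded or unblinded period-1 comparison.** With SD σ for one chart, the within-patient difference has SD σ√(2(1 − rho)), so the true difference is d × σ√(2(1 − rho)). Dividing by the SD relevant to each analysis:
- raw post-treatment values: d_b = d√(2(1 − rho));
- change from baseline: d_b = d at every rho;
- baseline as covariate: d_b = d√(2/(1 + rho)).

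The noncentrality is d_b/√(1/n₁ + 1/n₂), where the root is 0.437 for 10 v 11 and 0.343 for 17 v 17. Example, n = 21, rho = 0.5, raw: 0.65/0.437 = 1.49, power 29%. The chance that the estimate is below half the true effect is Φ(−1.49/2) = 23%; the chance that it is zero or wrong-signed is Φ(−1.49) = 7%.

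| Period-1 analysis, rho 0.3 to 0.8, both n | Power at 0.05 | Below half the true effect | Zero or wrong sign |
|---|---|---|---|
| Raw values | 39% to 15% | 19% to 32% | 4% to 18% |
| Change from baseline | 29% | 23% | 7% |
| Baseline as covariate | 42% to 32% | 18% to 22% | 3% to 6% |
| Planned crossover test | 81% | | |

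**4. Type I error if benefit can be claimed at the look.** The period-1 and final crossover Z statistics have correlation √((1 − rho)/2) on raw values: 0.59, 0.50 and 0.32 at rho 0.3, 0.5 and 0.8. The chance under the null that either crosses its boundary is:
- 0.05 at both looks: 8.8%, 9.1%, 9.5%;
- 0.001 at the look, then 0.05: 5.04%, 5.06%, 5.08%.

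With baseline as covariate the figures are 8.7% to 9.0% and about 5.05%. A rule that can only stop for futility never adds a rejection, so it causes no inflation.

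**The case against.** - **Boundaries may exist elsewhere.** This is a condensed article, and stopping limits often sit in an analysis plan or charter. The 0.05 appears in a sample size sentence; nothing says that the final test stays at 0.05 after an efficacy look. That stands. A reader might infer that the trial has no alpha control; all that can be said is that no threshold is stated here.
- **Error near 9% needs a lenient rule.** A reader might infer that the trial runs at that level. The wording about benefit being obvious suggests something much stricter than 0.05, and at 0.001 the cost is negligible.
- **Raw values are the wrong model.** The Abstract plans charts at baseline and after both phases, so a sensible first-period analysis would use baseline. That stands, and it lifts the low end of power from 15% to 29%. To say that the look carries almost no information would go too far.
- **No futility rule is given.** A reader might infer that a working treatment would often be stopped. The documents do not support a frequency: half the true effect is a yardstick chosen here. Assessing futility could also mean looking at variability, dropout and data completeness, which blinded data do show. But the text then makes futility a ground for termination, and says nothing to confine it to those matters.
- **Other routes to the data.** The article does not say that unblinding is allowed only for safety, the benefit clause is not expressly tied to this look, and the intended DMC could see unblinded data. All true. Still, no other interim or trigger is described, and the DMC is only an aim.
- **Crossover data would not all be lost.** With staggered entry, early patients may have finished period 2 by the time of the look. Correct, so a stop would discard only part of that information.

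**Conclusion.** The point holds as a conflict within the protocol, and as a look too weak for the decisions attached to it. Futility and obvious benefit are stated grounds for ending the trial; the one interim described is blinded and covers period 1 only; and Trial closure disagrees with itself on whether benefit counts. If the contrast were made visible, its power would be about 29-42% using baseline or 15-39% on raw values, against about 81% for the planned test, and its estimate would fall below half the true effect in about 18-32% of trials with the design effect true. These figures rest on the assumed rho of 0.3 to 0.8. Type I error ranges from about 5.1% to about 9.5% depending on an unstated threshold, and the upper figure is a worst case rather than a property of the plan. Should-fix.

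**What to change.** Limit the first-period interim to safety. In Trial closure and Monitoring, delete the task of assessing futility and the futility and benefit grounds for termination, including futility in the opening sentence of Trial closure, so that the two statements of grounds agree. The safety grounds are not affected by this point.

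If the sponsor wants to keep an efficacy stop, state a strict threshold (for example p < 0.001), have the independent DMC, once actually established, review it unblinded, and allow no futility stop on period-1 data. Assigning the stopping grounds to the DMC with pre-specified rules would also remove the blinding conflict, but a futility rule on this contrast would remain error-prone.

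The cost is protocol wording and the loss of an early stop in a small trial. If the look waits for the last patient to finish period 1, only about 10 weeks remain (a washout of about 4 weeks plus 6 weeks of period 2). At p < 0.001 the look would be crossed in only about 1% to 5% of trials with the design effect true, by the calculation in step 3, so little is given up.
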